### Trial monitoring

2.6

Trial monitoring is performed according to monitoring plan V 1.0, dated October 31, 2019. The study will be monitored by a trained monitor including 100% of informed consent and inclusion and exclusion criteria data, as well as monitoring of 100% of source data regarding the primary endpoint. Monitoring of trial data and documentation will ensure that protocol requirements, applicable local laws, ICH guidelines, and investigator obligations are fulfilled.

### Study-specific analysis and clinical measures

2.7

Blood samples for investigating functional cellular immunity, inflammatory response patterns, and course of organ (dys)function will be drawn preoperatively at baseline (visit 1), at ICU admission (visit 3), on postoperative day 1 (visit 4), and on postoperative day 3 (visit 5). In addition, blood samples will be stored for Biobanking (Liquid Biobank Bern). In addition, several clinical outcome parameters, and changes in organ dysfunction and necessity of organ support, will be followed up during hospital stay (Table 1). The primary outcome is measured by flow cytometry using a standardized mHLA-DR assay, as outlined above. ELISA measurements (Cube Dx, St. Valentin, Austria) will be performed using a multiplex ELISA technique. In addition, routine clinical and laboratory data (if available) are used to evaluate and/or to follow-up organ (dys)function(s), inflammation, and/or hemodynamics. Mortality (ICU, hospital, and during follow-up) is evaluated using hospital records, official registries, or other information.

### Analysis of results

2.8

The primary analysis will be performed on the full data set, that is, the intention-to-treat population. In an additional per-protocol analysis, we will exclude patients with major protocol deviations or missing primary outcome data.

We will apply a linear model corrected for the baseline value to analyze the mean change in quantitative expression of mHLA-DR (mAb/cell on CD14+ monocytes/macrophages) in patients treated with protocol A versus protocol B, namely the following quantity: 

, with 

 being the protocol A quantitative expression of mHLA-DR at times 1 and 3 respectively and 

 being the protocol B quantitative expression of mHLA-DR at times 1 and 3, respectively, and 

 being paired averages. We will assess the normality of model residuals and if the approximate normality is not satisfied we will use transformations of *Y*
_*ij*_ and *X*
_*ij*_ (with log or Box-Cox transformations). In case we do not achieve normality with any transformation we will use the Wilcoxon-Mann-Whitney test for comparing distributions of 

 and 

.

We will assess the AUC for the quantitative expression of mHLA-DR over time by computing the surfaces under the trajectories of quantitative expression of mHLA-DR and abscissa axis per subject, compute the averages per protocol group, and compare these averages either with an unpaired *t* test (eventually with transformations for normality) or a nonparametric Wilcoxon-Mann-Whitney test.

We will compare the average protocol trajectories of the quantitative expression of mHLA-DR, inflammatory markers, and organ dysfunction by fitting the following mixed-effects model: 

 (baseline value is added as a covariate) with *i* being the subject; *j* the protocol; *t* the time-point 2, 3, or 4; *G*
_*ij*_ the protocol corresponding to subject *i*; *X*
_*ij*_ is the quantitative expression of mHLA-DR at time 1; *T*
_*it*_ the time-point 2, 3, or 4 for subject *i*, *ε*
_*ijt*_ residuals, and *α*
_*i*_ random effect capturing the individual variability of subject *i*. Testing the hypothesis *γ*
_4_ = 0 is equivalent to testing the protocol effect over time under assumption of good model fit.

We will provide descriptive statistics for, for example, length of ICU and hospital stay (days after surgical interventions), and cumulative TISS points (resource need) and compare groups by the nonparametric Wilcoxon-Mann-Whitney test. We will show proportions of ICU mortality, hospital mortality, and 28-day mortality and compare groups calculating a risk difference and applying a chi-square test.

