### Population and sample size calculation

2.4

Fifty-four patients undergoing planned surgical treatment for IE will be randomly allocated (1:1 allocation) to receive either best standard of care plus cytokine adsorption (protocol A) or best standard of care alone (protocol B). Allocation to the groups, protocol A or protocol B, is done computerized using the REDCap software. The null hypothesis is that there is no differences in mHLA-DR expression (readout: monoclonal antibodies [mAb/cell]) between the 2 groups. Assuming the response to be normally distributed within each subject group with a standard deviation of 3200 mAb/cell and a true difference in the arms means of 2500 mAb/cell (10,000 vs 7500 mAb/cell of mHLA-DR expression), n = 27 patients will be required to be able to reject the null hypothesis that the population means of the experimental and control groups are equal with probability (power) of 0.8. The type I error probability associated with this test of this null hypothesis is 0.05 (2 sided).

The following inclusion criteria apply:

1.Subjects scheduled for cardiac surgery for infectious endocarditis (according to DUKE criteria) with antibiotic therapy for ≤14 days.2.Presence of informed consent3.Age ≥18 years.

The following exclusion criteria apply:

1.Known previous treatment (last 6 months) with immunologically active biologicals or specific immunomodulatory drugs (e.g., rituximab).2.Known high-dose chronic (i.e., before onset of infectious endocarditis) steroid medication with prednisone equivalent of >30 mg/day.3.Patients on extracorporeal membrane oxygenation (ECMO), or any other (preoperative) cardiac assist device.4.Moribund patient (life expectancy <14 days, as judged by investigator).

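### The primary analysis is picked from the trial's own outcome residuals, so its scale and target are not fixed in advance, and its last step is a rank test that drops baseline as a covariate

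*Protocol article*

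**What the plan says.** Protocol article, section 2.5.2, defines the primary endpoint as the change in mHLA-DR from baseline (visit 1) to day 1 after surgery (visit 4). Section 2.8 analyses it with a linear model corrected for baseline, then sets a sequence of replacements:

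- After inspection of the model residuals, "if the approximate normality is not satisfied we will use transformations of" the outcome and baseline values, by log or Box-Cox.
- If that fails: "In case we do not achieve normality with any transformation we will use the Wilcoxon-Mann-Whitney test for comparing distributions of" two quantities. Their formulas did not survive in the text available, so it cannot be seen whether they are changes or day 1 values.

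Section 2.4 sizes the trial as a comparison of two means of a normally distributed response, "with a standard deviation of 3200 mAb/cell and a true difference in the arms means of 2500 mAb/cell" ("10,000 vs 7500 mAb/cell of mHLA-DR expression"), with 27 patients per arm (54 in total), a two-sided type I error of 0.05, and the aim of rejecting the hypothesis that "the population means of the experimental and control groups are equal with probability (power) of 0.8". No correlation between baseline and day 1 is given.

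**The concern.** Each branch answers a different question. The raw-scale model estimates a baseline-adjusted mean difference in mAb/cell. The log model estimates a ratio. A Box-Cox model estimates a difference on a scale whose exponent comes from the data. The Wilcoxon-Mann-Whitney test compares two distributions. Only the first corresponds to the effect in section 2.4. Which of them becomes the primary result depends on the residuals of the very model that compares the arms, in a trial where only the subject is blinded (section 2.3).

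The last branch is also a plain two-sample test. It leaves out the baseline covariate that the first-choice model contains, although a rank method that keeps baseline is available. At stake are a primary result whose meaning is settled only after the data are in, and power given up for no benefit if the fallback is reached.

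**Working it through.** **Inputs from section 2.4:** difference 2500, SD 3200, two-sided alpha 0.05, power 0.80, 27 per arm.

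**Assumptions, because the documents are silent:** SD 3200 at both visits; baseline to day 1 correlation ρ varied from 0 upward; errors normal, t(5) or t(3), all scaled to the same SD. The heavy-tailed cases matter because the fallback is meant for residuals that do not look normal.

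**Step 1. The plan's own figure.** Standardised difference = 2500/3200 = 0.781. The normal approximation gives 2 × (1.960 + 0.842)² / 0.781² ≈ 25.7, so 26 per arm. The noncentral t calculation gives 26.7, so 27 per arm, with power 0.804. The stated 27 reproduces.

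**Step 2. First-choice model.** Residual SD = 3200 × √(1 − ρ²). At ρ = 0.3 this is 3200 × √0.91 ≈ 3053. Power under normality is 0.80, 0.84 and 0.90 at ρ = 0, 0.3 and 0.5, so it is never below plan.

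**Step 3. Wilcoxon on changes.** SD of the change = 3200 × √(2(1 − ρ)). At ρ = 0.3 this is 3200 × √1.4 ≈ 3786. The efficiency of Wilcoxon under normality is 3/π ≈ 0.955, so the effective size is 27 × 0.955 ≈ 25.8 per arm. Power is 0.49, 0.64 and 0.785 at ρ = 0, 0.3 and 0.5 (simulated, 20,000 runs: 0.49, 0.63, 0.78). It crosses 0.80 at ρ of about 0.52. In simulations with heavier tails the crossing is at about 0.44 for t(5) and 0.25 for t(3).

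**Step 4. Wilcoxon on day 1 values.** The SD stays 3200, so power under normality is about 0.78 whatever ρ is. With t(5) or t(3) errors it is 0.83 to 0.96. There is no correlation threshold in this case.

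**Step 5. Fallback options side by side** (ρ = 0.3, 27 per arm, 3000 simulated trials; Monte Carlo standard error at most about √(0.64 × 0.36/3000) ≈ 0.009):

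| Analysis | Normal | t(5) | t(3) |
|---|---|---|---|
| Wilcoxon on changes | 0.64 | 0.69 | 0.84 |
| Wilcoxon on day 1 values | 0.77 | 0.85 | 0.95 |
| Rank-ANCOVA with baseline | 0.81 | 0.88 | 0.96 |

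Rank-ANCOVA matched or beat both Wilcoxon versions, within simulation error, at correlations from 0 to 0.7.

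**Step 6. The sequence as a whole.** The article sets no normality criterion, so a Shapiro-Wilk test at 0.05 was assumed, with Wilcoxon on changes as the last step. At ρ = 0.3, with a log step (5,000 runs):

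- Type I error was 0.045 (normal) and 0.054 (t(3)).
- Power was 0.83 (normal) and 0.87 (t(3)).
- The Wilcoxon branch was reached in about 4% of normal and 60% of t(3) datasets.

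Without a transformation step, power for normal/t(5)/t(3) was 0.83/0.81/0.87 at ρ = 0.3, 0.89/0.90/0.95 at ρ = 0.5 and 0.79/0.74/0.77 at ρ = 0.

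**The case against.** The order of the steps is written down in advance, and no material inflation of type I error was found. A normality criterion and an effect measure for each branch are details that an analysis plan commonly supplies, and that plan is not shown. A rank fallback exists to withstand heavy tails, and it does: with t(3) errors and ρ = 0.5, Wilcoxon on changes reaches about 0.94 against about 0.90 for raw-scale ANCOVA. The trial also calls itself a pilot whose findings need multicentre confirmation.

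Much of this stands, and it rules out several stronger readings:

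- A reader might infer that the trial loses its 0.80 power whenever the baseline correlation is below about 0.5. The documents do not support that. The figure needs normal data, which rarely reach the fallback, and it needs changes to be the quantities compared, which cannot be confirmed.
- A reader might call the fallback unadjusted for baseline. If changes are compared, baseline is still subtracted. What is lost is baseline as a covariate.
- A reader might call Wilcoxon the least efficient choice. The t(3) result above shows otherwise.

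What the objection does not remove is the rule itself. The article states that residuals decide which analysis is primary. Writing the order down does not fix what is estimated, and tolerance of heavy tails does not require giving up the covariate. The missing criterion and effect measures are not counted as faults here.

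**Conclusion.** The point holds in a limited form. Section 2.8 leaves the scale and quantity of the primary result open until outcome residuals are seen, and only its raw-scale branch corresponds to the 2500 mAb/cell mean difference in section 2.4. If the fallback is reached, it gives up power that a rank method with baseline would keep. At an assumed ρ of 0.3 the loss is about 0.12 to 0.19 if changes are compared (0.96 − 0.84 to 0.88 − 0.69), and about 0.01 to 0.04 if day 1 values are compared (0.96 − 0.95 to 0.81 − 0.77).

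For the plan as a whole the effect on power is modest: about 0.80 or more at correlation 0.3 and above, and about 0.74 to 0.80 at correlation 0. The false-positive rate is not at issue. The power figures rest on SD 3200 at both visits, the assumed correlations and error distributions, and, for the whole sequence, on a Shapiro-Wilk gate at 0.05 and Wilcoxon on changes. The unfixed estimand depends on none of these.

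**What to change.** Before outcome data by arm are seen, name one primary analysis: ANCOVA of visit 4 mHLA-DR on protocol and baseline, on one prespecified scale, with permutation or heteroscedasticity-robust p value and confidence interval, so that no normality gate is needed. Raw mAb/cell matches the sample size calculation. Report the transformed-scale, rank-ANCOVA and Wilcoxon results as sensitivity analyses.

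If the sponsor prefers to keep a rank fallback, replace the Wilcoxon test by rank-ANCOVA with baseline. That restores the covariate but leaves the target dependent on the residuals, so it is the second choice.

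The cost is a change of wording and slightly more analysis work, with no extra patients, visits or assays. The statistical downside is somewhat lower power than a rank method if tails are heavy: with t(3) errors and ρ = 0.3, about 0.87 for raw-scale ANCOVA against 0.96 for rank-ANCOVA. That is still above the planned 0.80.

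### If gamma4 is the protocol-by-time term, the trajectory model's only named test cannot detect a constant post-operative benefit and does not test the protocol effect

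*Protocol article*

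**What the plan says.** Section 2.8 (Analysis of results) introduces the model as follows: "We will compare the average protocol trajectories of the quantitative expression of mHLA-DR, inflammatory markers, and organ dysfunction by fitting the following mixed-effects model". The responses are at time-points 2, 3 and 4. Baseline (time-point 1) enters as a covariate, and each patient has a random effect. The variables are listed in the order protocol, baseline, time. One hypothesis is named, gamma4 = 0, and testing it "is equivalent to testing the protocol effect over time under assumption of good model fit".

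Section 2.7 gives four blood samples: pre-operative, ICU admission, day 1 and day 3. Time-points 2, 3 and 4 are therefore read here as ICU admission, day 1 and day 3. This agrees with the primary analysis, which uses times 1 and 3 for a baseline-to-day-1 endpoint.

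Section 2.5.3 defines secondary endpoint 1 as the change in mHLA-DR to visit 4 and to day 3. Endpoints 3 and 4 are the changes in inflammatory markers and in SOFA scores from before surgery to days 1 and 3.

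For mHLA-DR, section 2.8 also gives a baseline-adjusted day-1 comparison (primary) and a between-group comparison of AUC. For inflammatory markers and organ dysfunction it describes only the mixed model.

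**The concern.** Adsorption takes place once, during bypass, so every modelled response comes after the intervention. With baseline as a covariate, a difference already present at ICU admission belongs to the protocol main effect. The interaction measures only how that difference changes afterwards. A test of the interaction alone is a test of parallel curves, and good model fit does not turn it into a test of the protocol effect.

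The test also does not match the endpoints. Endpoints 3 and 4 are changes to particular days, so the relevant quantities are the between-arm differences at those days. A sustained effect on IL-6 or SOFA at every visit could give a null result on the only test named for those outcomes.

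**Working it through.** **Inputs from section 2.4.** "a true difference in the arms means of 2500 mAb/cell"; "standard deviation of 3200 mAb/cell"; "n = 27 patients will be required" (per arm, 54 in total); two-sided 5% level; rejection "with probability (power) of 0.8".

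**Assumptions.** gamma4 is protocol-by-time. The SD is 3200 at each visit, with equal correlation r between visits. The documents give no r, so 0.3 to 0.7 is used. Data are complete. The power formulas use normal or chi-square approximations and leave out the gain from baseline adjustment.

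**The plan's own figure.** n = 2 × (1.960 + 0.842)² × 3200² / 2500² = 25.7, so 26 per arm. The noncentral t calculation gives power 0.789 at 26 and 0.804 at 27. The stated 27 per arm is reproduced. No power is stated for the trajectory model.

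**Constant benefit (2500, 2500, 2500).** Every interaction contrast is a difference between visit-specific differences, and 2500 − 2500 = 0. So gamma4 = 0 exactly, whether time is linear or categorical, and the test rejects at its 5% level. A simulation of 20,000 runs at r = 0.5 gave 0.051.

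The average difference has SE = √[(2/27) × 3200² × (1 + 2r)/3]. The 3-df joint test of the protocol main effect and both interaction terms has noncentrality (2500/SE)² for this pattern.

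| r | SE | 2500/SE | Power, average difference | Power, 3-df joint |
|---|---|---|---|---|
| 0.3 | 636 | 3.93 | 0.976 | 0.925 |
| 0.5 | 711 | 3.52 | 0.940 | 0.852 |
| 0.7 | 779 | 3.21 | 0.894 | 0.775 |

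With baseline adjustment, the simulated power of the average-difference test was 0.99.

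The zero does not depend on the scale of the outcome. The powers apply to any outcome with a constant difference of 2500/3200 = 0.78 SD.

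**Day-1 peak (0, 2500, 0), only if time is a linear score.** With codes 2, 3, 4 the slope weights are (−1/2, 0, +1/2), so the slope is 0 and rejection is 5% (simulated 0.048). With days 0, 1, 3 the mean is 4/3 and the sum of squares is 42/9. The day-1 weight is (−1/3)/(42/9) = −0.071, the slope is −178.6, and rejection is 8 to 13%. With categorical time, the 2-df interaction has power 0.71 to 0.98 and the 3-df joint test 0.74 to 0.97. The average-difference test has only 0.19 to 0.26 for this pattern.

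**Asymmetric peak (1500, 2500, 0), linear time.** The slope with codes is (0 − 1500)/2 = −750. Power is 0.31 to 0.60 with codes and 0.44 to 0.79 with days.

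**The case against.** **The identity of gamma4 is inferred.** The equation is missing from the text reviewed, which is no fault of the plan. With an intercept numbered zero and the terms in listed order, the fourth coefficient is naturally protocol-by-time, and the phrase about an effect over time fits that. With the intercept numbered one, that order would make gamma4 the time effect, which tests no protocol effect at all. With some other ordering it could be the protocol main effect, and the point would then fall away. The sponsor can settle this from its own equation.

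**The wording allows a milder reading.** An effect over time, in a paragraph about trajectories, can mean a differing time course, which an interaction does test. But the plan then names no test of whether inflammatory markers or organ dysfunction differ between arms, so the gap remains.

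**mHLA-DR has other analyses.** This stands. The primary day-1 model detects a constant or symmetric-peak benefit of 2500 with power of about 0.89 (baseline correlation 0.5 assumed). The AUC comparison addresses the overall level, although its power was not computed. Only the day-3 change lacks its own comparison.

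**A reader might infer that any benefit peaking on day 1 is missed.** The documents do not support that. It needs linear time and a roughly symmetric peak. The text does not state the coding, although a single coefficient suggests linear.

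**A reader might also infer that a null gamma4 will be reported as absence of any protocol effect.** The protocol states no such rule.

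**Time coding is commonly left to an analysis plan.** That is fair, and its absence is not the finding. The equivalence statement is printed in the article and is what needs correcting.

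**Conclusion.** On the most plausible reading of gamma4, the equivalence statement is wrong as written. For a constant 2500 mAb/cell difference the named test rejects at about 5%, where a test of the average difference has power 0.89 to 0.98. The blindness to a constant effect needs no assumption about time coding or correlation. The power range rests on r of 0.3 to 0.7 and a common SD of 3200.

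The consequence is limited to secondary analyses: inflammatory markers, organ dysfunction and the day-3 mHLA-DR change. It would be an overreading to say that the trial's main result is at risk, because the primary endpoint, its sample size and its error rate do not depend on this model. The point should be corrected before analysis, but it does not rank with a defect in the primary analysis.

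**What to change.** - Show which term gamma4 multiplies and how time is coded.
- Enter time as a three-level factor (ICU admission, day 1, day 3), with protocol, protocol-by-time terms and baseline.
- Test the protocol effect jointly: main effect plus both interaction terms, 3 df.
- Report the baseline-adjusted protocol difference with its CI at each visit. This also matches secondary endpoints 1, 3 and 4.
- Keep the interaction only as a test of whether the effect changes over time, and reword the equivalence sentence to say so.

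The cost is wording and two more parameters than a linear-time model, with no new data or patients. The joint test gives up some power for a constant effect (0.775 to 0.925, against 0.89 to 0.98 for the average difference). In return it keeps 0.74 to 0.97 for a day-1-only effect, where the average-difference test has 0.19 to 0.26.

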## Introduction

1

Infective endocarditis (IE) is a life-threatening clinical condition that is characterized by infection of the endo-(myo)cardium and cardiac valves.^[1]^ IE treatment depends on the severity of the infection and induced tissue damage. As first-line clinical therapy, systemic intravenous antibiotic treatment according to international guidelines is applied.^1^,^2^ In severe IE affecting the function of heart valves, surgical repair and replacement can be deemed necessary. The decision when to operate on a patient is based on internationally approved guidelines^[2]^ and depends on expected or observed complications, severity of valve dysfunction, and size of vegetation(s).^[1]^ The aim of surgery is to control the site of infection and to restore (normal) heart function while repairing or replacing the infected valve and to repair associated defects (abscess). During cardiac surgery itself, the use of a cardiopulmonary bypass circuit is required.

Severe infections, such as IE, are known to induce significant changes in a hosts’ immune response.^3^,^4^,^5^,^6^,^7^ In fact, numerous patients with IE develop a persistent functional immunological phenotype that can best be characterized by a profound anti-inflammation and functional immunological anergy.^3^,^5^,^8^ This seems especially the case in patients with unresolved infectious foci and was previously referred to as “injury-associated immunosuppression” (IAI).^[3]^ IAI can be assessed by measurement of the monocytic human leukocyte antigen-DR (mHLA-DR) expression, a standardized “global” biomarker of immune competence.^8^,^9^ Persistence of IAI is associated with prolonged intensive care unit (ICU) length of stay, increased secondary infection rates, and death.^[3]^

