#### Secondary endpoints

2.5.3

1.Change in mHLA-DR from baseline (pre-OP) to post-OP (visit 4) and day 3 (visit 5) post-OP.2.Area under the curve (AUC) of quantitative mHLA-DR expression between baseline (pre-OP), ICU admission, and days 1 (visit 4) and 3 (visit 5) post-OP.3.Change in inflammatory markers including cytokines (including white blood count, C-reactive protein, interleukin 6 [IL-6], IL-10, multiplex enzyme-linked immunosorbent assay, inflammatory markers) and immune cell phenotype (flow cytometry) from pre-OP to days 1 (visit 4) and 3 (visit 5) post-OP.4.Change in organ dysfunction (Sequential Organ Failure Assessment scores including subscores) from baseline (pre-OP) to days 1 (visit 4) and 3 (visit 5) post-OP.5.Length of ICU/hospital stay (days after ICU admission) and total days in hospital.6.Cumulative Therapeutic Intervention Scoring System (TISS) points (resource need) while on ICU.7.ICU-, hospital-, 28-day, 60-day, and 90-day mortality.8.Total amount of infused fluids on ICU; including number and type of transfusions.9.Duration of vasoactive drug therapy, cum. vasopressor dose.10.Length of invasive mechanical ventilation (intubation to extubation), renal function (secondary) ECMO, or other circulatory supporting systems.

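### Length of stay has two different time origins, and the Wilcoxon comparison of stay and TISS has no rule for deaths, so observed values would favour an arm with more early deaths

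*Protocol article*

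**What the plan says.** **Definition of stay.** Section 2.5.3 (Secondary endpoints), item 5, reads "Length of ICU/hospital stay (days after ICU admission) and total days in hospital". Section 2.8 (Analysis of results) describes the same outcome as "length of ICU and hospital stay (days after surgical interventions" and does not mention total days in hospital.

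**TISS.** Section 2.5.3, item 6, is "Cumulative Therapeutic Intervention Scoring System (TISS) points (resource need) while on ICU". Accrual therefore stops when the patient leaves the ICU, alive or dead.

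**Test.** Section 2.8 plans descriptive statistics for stay and TISS and a two-group rank test: "cumulative TISS points (resource need) and compare groups by the nonparametric Wilcoxon-Mann-Whitney test". It does not say whether a patient who dies enters at the observed value, takes the worst rank, or is left out.

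**Mortality.** Section 2.5.3, item 7, lists "ICU-, hospital-, 28-day, 60-day, and 90-day mortality". Section 2.8 handles ICU, hospital and 28-day mortality separately: "compare groups calculating a risk difference and applying a chi-square test".

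**Link between stay and death.** The Introduction states: "Persistence of IAI is associated with prolonged intensive care unit (ICU) length of stay, increased secondary infection rates, and death".

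**The concern.** There are two problems.

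**Time origin.** One endpoint is counted from two different starting points. They differ for anyone in the ICU before the operation, if that pre-operative admission is the one counted. In that case the count in 2.5.3 includes days before the randomised treatment could act. Leaving both in place also leaves a choice that could be made after the data are seen.

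**Deaths.** Death cuts short ICU stay, hospital stay and TISS accrual. If the rank test is applied to raw values, a patient who dies on day 1 gets one of the most favourable ranks. The Introduction links persistent immunosuppression both to longer ICU stay and to death, so the mechanism under study could move survival and raw stay in ways that cancel or mislead. An arm with more early deaths could appear to have shorter stay and lower resource need. The pilot is meant to inform later multicentre work, so its clinical signals should point the right way.

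**Working it through.** **Time origin.** Set side by side, 2.5.3 counts from ICU admission and adds total hospital days, while 2.8 counts from surgery. Section 2.7 places the ICU-admission sample (visit 3) after the pre-operative baseline (visit 1), which suggests that post-operative admission is meant. On that reading the two counts differ only by the time between surgery and arrival in the ICU. If an earlier admission counts, they differ by the pre-operative ICU stay. Section 2.4 does not exclude patients already in the ICU, and the article does not say how many there are.

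**Deaths: inputs.** From the article: 54 patients, 1:1, so 27 per arm. (That figure reproduces: a difference of 2500 with SD 3200, two-sided 5% and 80% power gives 26.7, so 27 per arm by t test, with power 0.804.) There is no planned figure for stay or mortality to reproduce. Everything else below is assumed.

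**Closed form.** Let pA and pB be the proportions dying early, with equal stay distributions otherwise. If every early death is shorter than every survivor's stay:

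- observed values: P(stay A > stay B) = (1−pA)·pB + 0.5·(1−pA)(1−pB) + 0.5·pA·pB = 0.5 − (pA−pB)/2
- deaths ranked worst: 0.5 + (pA−pB)/2

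For 20% against 10% this gives 0.45 and 0.55. For 30% against 10% it gives 0.40 and 0.60. In counts, with 4 of 27 early deaths in A and none in B, P(A shorter) = 4/27 + (23/27)×0.5 = 0.574 with observed values, and (23/27)×0.5 = 0.426 with deaths ranked worst.

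**Simulation, early deaths.** 27 per arm, 6000 runs; stay log-normal, median 12 days, log-SD 0.7, identical in both arms; deaths uniform over 0.5 to 5 days; two-sided Wilcoxon-Mann-Whitney test at 5%. The last two columns give the share of trials in which A has significantly shorter stay (nominal 2.5%).

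| Mortality A / B | P(stay A > stay B), observed | Observed values | Deaths ranked worst |
|---|---|---|---|
| 10% / 10% | 0.50 | 2.5% | 2.3% |
| 15% / 10% | 0.48 | 4.5% | 1.0% |
| 20% / 10% | 0.45 | 8.1% | 0.4% |
| 30% / 10% | 0.41 | 21.7% | 0.03% |

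The simulated probabilities agree with the closed form. With equal mortality there is no tilt.

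**Simulation, timing of death.** 27 per arm, 4000 runs; stay median 6 days, log-SD 0.8; 4 deaths in A, none in B; a patient who dies is assumed to stay in the unit until death. Share significantly favouring A:

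| Time of death | Favours A |
|---|---|
| no deaths | 2.2% |
| 0.2 to 1 day | 12.2% |
| 1 to 5 days | 7.0% |
| 1 to 14 days | 1.9% |
| 1 to 28 days | 0.7% |

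With all deaths within a day but a 3-to-1 split, the figure is 4.7%; with 3 to 2 it is 2.0%. The tilt therefore needs deaths that are both early and unequal between arms.

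**The case against.** **Silence is not a statement.** A reader might infer that the plan counts deaths as short stays. It does not say so. The Wilcoxon test is equally compatible with worst ranks or a survivors-only comparison, and the full protocol or an analysis plan may hold the rule. This stands. The point is only that the article names a test and no scoring rule, and that the endpoints taken at face value give the unfavourable scoring. The contradiction on the time origin has no such excuse, because the article states both versions.

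**Scope.** A reader might extend the point to ventilation and vasopressor duration. Section 2.8 names no test for them, so the documents do not support that.

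**Size.** It is tempting to conclude that any survival harm would look like a benefit, or to quote the 12% figure as typical. Neither holds. That figure needs four deaths against none, all within a day, and later deaths remove or reverse the effect. The exclusion of patients judged "Moribund patient (life expectancy <14 days, as judged by investigator" makes very early deaths less likely.

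**Visibility.** Mortality is reported by arm beside these endpoints, so a large imbalance would be seen. This limits the harm but does not correct the comparison of stay.

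**TISS.** The endpoint is labelled as resource need. The observed total, including patients who die, is a legitimate measure of that, and ranking deaths worst would stop it measuring resources. This stands and shapes the fix.

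**Conclusion.** The point holds in a limited form. The time origin of stay is contradictory between 2.5.3 and 2.8 and must be reconciled. It does not follow that the 2.5.3 count certainly contains pre-treatment days: that depends on which ICU admission is meant, and the practical difference is probably small for patients who go straight from theatre to the ICU.

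For deaths, the only named comparison has no scoring rule, and observed values would tilt it towards an arm with more early deaths. With the assumed inputs (stay log-normal with median 12 days, deaths within 0.5 to 5 days) the tilt is small for a 5-point mortality difference (about 4.5% against 2.5%) and larger for 10 to 20 points (about 8% to 22%). It is absent with equal mortality, and absent or reversed with late deaths. None of these inputs comes from the article. Only secondary endpoints of a self-described pilot are concerned; the mHLA-DR primary endpoint is unaffected.

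**What to change.** 1. Use one time origin, end of surgery, for ICU and hospital stay in both 2.5.3 and 2.8. If total days in hospital is kept, define it as a separate descriptive count.
2. Compare ICU-free and hospital-free days to day 28, with death by day 28 set to 0, or else rank deaths worst for stay. Keep the Wilcoxon-Mann-Whitney test. If the full protocol or an analysis plan already holds a rule for deaths, state it in 2.8.
3. Show mortality and raw stay in survivors alongside, the latter as description only, because survivors are a group selected after randomisation.
4. Keep cumulative TISS as observed resource use, report it with mortality, and state that a lower total is not read as benefit.

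The cost is wording. 28-day mortality and length of stay are already listed endpoints, so little or no new data should be needed. The downside is that the stay endpoint becomes a composite with survival, which is why its components must be shown.
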